### Bias

We expect a percentage of women to drop out of the study before its end, especially in the case group. Mothers who experience a denial of pregnancy are more likely to drop out of the study earlier than mothers in the control group. This early attrition will impact the size of our sample.

### Coding

The attachment pattern of the mother (AAN) and of the infant (Strange Situation) and the mother-infant interactions (CIB) will be all evaluated based on videos conducted by each center. Ratings will be performed by one single qualified team (principal investigator center) and by two trained raters who will remain blind to group status.

### Statistical methods

Data will be described using means and standard deviations for quantitative variables and numbers and percentages for qualitative variable. Normal distributions will be checked.

To study factors associated with pregnancy denial, characteristics of women with pregnancy denial and characteristics of women without pregnancy denial will be compared with univariate analysis (using Student’s t, Wilcoxon, chi-square or Fisher’s exact tests, as appropriate) and multivariate analysis (logistic regression).

Factors associated with the attachment pattern of the child, divided into two categories (“secure” and “insecure”), will be studied by univariate (Student’s t, Wilcoxon, chi-square or Fisher’s exact tests, as appropriate) and multivariate analysis (logistic regression).

A *P*-value <0.05 will be considered statistically significant.

All analysis will be performed using SAS version 9.4 (SAS Inc., Cary, NC, USA).

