**Methods:**

The design is a case-control prospective study, which will compare two groups of mother-infant dyads: a “case” group with maternal denials of pregnancy and a “control” group without denials of pregnancy. A total of 140 dyads (mother + infant) will be included in this study (70 cases and 70 controls) and followed for 18 months. The setting is a national recruitment setting with 10 centers distributed all over France. The follow-up of the “cases” and the “controls” will be identical and will occur over 5 visits. It will include measures of the infant attachment pattern, the quality of early mother-infant interaction and infant development.

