### Study design and setting

This study entitled “Attachment and pregnancy denial” is a national multicenter prospective case-control study with 13 French investigation centers (Anthony Ile-de-France, Besançon, Bordeaux, Nancy, Paris Bichat, Paris La Pitié Salpêtrière, Reims, Strasbourg, Toulouse, Amiens, Troyes, Aubagne, Lille).

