### Population

*Inclusion criteria* are as follows. In the case group, dyads are composed of a woman with pregnancy denial and her infant. Pregnancy denial will be defined by a pregnancy announcement after 20 weeks of gestation and a lack of objective perceptions of the pregnancy by the woman. Women with no follow-up of the pregnancy due to geographical, social or administrative reasons (absence of insurance coverage, family conflicts, unemployment, and pregnancy hidden to the employer) will not be included. In the control group, dyads are composed of a woman without pregnancy denial and her infant. The case group and the control group will be matched on primiparous and non-primiparous mothers and on premature (birth before 37 GW) and non-premature infants.

*Exclusion criteria* are as follows: minor women (< 18 years old), women with intellectual disability, women with an acute or chronic psychotic condition, women who do not speak fluent French, women with illegal administrative status, newborn with a life-threatening prognosis, newborn with an organic malformation and/or genetic abnormality observed before leaving the hospital, and medically assisted reproduction (for the control group).

In a pragmatic way, due to the lack of data concerning the relationship between pregnancy denial and infant attachment pattern in the literature, participation will be proposed to all women with pregnancy denial during the inclusion period. Given the average number of births per year and by center (2500 on average), the number of participating centers (N=13), the frequency of pregnancy denial (2/1000 child births), the duration of the inclusion phase (48 months) and the expected participation acceptance rate (25%), 70 women with pregnancy denial will be included in this study. Therefore, 140 dyads mother-infant women will be included in this study. Based on the hypothesis of a score for disorganization [22, 23] of 3.44 ± 1.90 in the control group, inclusion of 70 dyads mother-infant per group (and evaluation of 50 dyads at 18 months because of lost of follow up) will highlight a score for disorganization of 2.37 in the case group, with a signification of 5%, a power of 90% and a bilateral (NQuery Software 7.0).

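### Cases and controls are matched on parity and prematurity, but the stated analyses do not say that the matching is accounted for

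*Protocol article*

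**What the plan says.** The article describes a "national multicenter prospective case-control study with 13 French investigation centers", with 70 cases (denial) and 70 controls. Under Population, the groups "will be matched on primiparous and non-primiparous mothers and on premature (birth before 37 GW) and non-premature infants". This gives two binary factors and four cells. The article does not say whether each control is matched to a particular case or the groups are balanced by frequency.

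Under Statistical methods, "characteristics of women with pregnancy denial and characteristics of women without pregnancy denial will be compared with univariate analysis" with t, Wilcoxon, chi-square or Fisher tests, and then with logistic regression. A second paragraph applies the same set of methods to factors associated with the child's attachment, classed as secure or insecure. Neither paragraph mentions the matching, names a paired, stratified or conditional method, or lists the model covariates.

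On follow-up, the article plans "inclusion of 70 dyads mother-infant per group (and evaluation of 50 dyads at 18 months because of lost of follow up"). Its Bias section expects mothers with denial to leave the study earlier than control mothers.

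**The concern.** Matching is a design decision that the analysis should follow. In the denial analysis, controls are selected to share the cases' mix of parity and prematurity. If a maternal factor such as insecure attachment or a personality disorder is also related to parity or prematurity, that selection makes the exposure distribution of controls resemble that of cases. A crude odds ratio then lies closer to 1 than the odds ratio within matching cells, and its standard error is too large. This bears on a stated secondary objective, the factors associated with denial, studied with only 70 cases.

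The infant-outcome comparison is different. There denial is the exposure and the matched groups are followed forward, as in a matched cohort. The toward-1 selection argument does not carry over. What is at stake is precision, because variation explained by the matching factors stays in the error term, and balance, because matching at inclusion does not guarantee balance among the dyads seen at 18 months.

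**Working it through.** **The plan's own figure.** The article gives no figure for the effect of matching. The nearest is its power statement: 3.44 against 2.37, SD 1.90, two-sided 5%, power 90%. For two independent groups, n = 2 × (1.96 + 1.2816)² × (1.90/1.07)² = 66.3, so 67 per group. Power is 91.5% at 70 per group and 80.4% at 50. The 90% therefore fits an unmatched comparison of the 70 included, not of the 50 evaluated. That shortfall is a separate matter. It does not settle how matching was treated: a paired t-test on 50 pairs would also reach 90% with a within-pair correlation of about 0.25 to 0.30, which the article does not state.

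**Odds ratio for a denial risk factor.** The documents give none of the inputs below, so all are assumptions: 45% primiparous, 15% preterm, the two independent, exposure in about 40% of controls, and exposure related to each matching factor by an odds ratio g.

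1. Cell weights: neither factor 0.55 × 0.85 = 0.4675; preterm only 0.55 × 0.15 = 0.0825; primiparous only 0.45 × 0.85 = 0.3825; both 0.45 × 0.15 = 0.0675. Matching makes these the same in cases and controls.
2. Exposure in controls: logit p0 = ln(0.4/0.6) + ln(g) × [(a − 0.45) + (b − 0.15)], with a and b the 0/1 indicators for primiparous and preterm. In cases: logit p1 = logit p0 + ln(2.5).
3. Crude odds ratio: [P1/(1 − P1)] ÷ [P0/(1 − P0)], where P0 and P1 are the weighted sums of p0 and p1 over the cells.

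Worked case, g = 3: p0 is 0.2564 with neither factor, 0.5085 with either one and 0.7563 with both, so P0 = 0.4074. The matching p1 values are 0.4630, 0.7212 and 0.8858, so P1 = 0.6116. The odds are 1.5745 and 0.6874, and their ratio is 2.29 instead of 2.5.

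| g | Odds ratio ignoring matching (true 2.5) | Shrinkage of log odds ratio |
|---|---|---|
| 1 | 2.50 | 0 |
| 1.5 | 2.47 | about 1.5% |
| 2 | 2.41 | about 4% |
| 3 | 2.29 | about 10% |
| 5 | 2.12 | about 18% |

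If the true odds ratio is 1, the crude one is also 1 at every g.

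A simpler set of assumptions gives the same direction. With two equal-sized strata and a true odds ratio of 3, control exposure of 30/50%, 20/60% and 10/60% gives crude values of 2.86, 2.48 and 2.13. These prevalences imply exposure-by-stratum odds ratios of 2.3, 6 and 13.5, so the last two are strong associations.

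**Standard errors and choice of model.** A simulation used 1,500 runs of 70 matched pairs under the same assumptions.

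- g = 3, true odds ratio 1: the unadjusted model had mean standard error 0.347 against an empirical SD of 0.318, and rejected in 2.9% of runs at nominal 5%. With the two factors as covariates the figures were 0.369, 0.360 and 3.8%.
- g = 1.5, true odds ratio 1: the unadjusted standard error was about right (0.348 against 0.361; 5.6% rejection).
- g = 3, true odds ratio 2.5: median estimates were 2.28 unadjusted, 2.56 adjusted and 2.55 conditional on pairs. Rejection was 70.8%, 73.9% and 71.0%.

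**Infant outcomes.** The plan allows for 20 of 70 dyads lost per group (29%) and expects earlier loss among cases. The documents do not say how loss relates to parity or prematurity, so no size can be given for the resulting imbalance.

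**The case against.** The strongest objection is that the article names logistic regression without listing covariates, so parity and prematurity are neither included nor excluded, and a condensed article may leave that list to its analysis plan. This stands. A reader might infer that the logistic model ignores the matching; the text does not show it. If both factors are in the model, ordinary logistic regression handles four cells adequately, as the 2.56 against 2.55 shows. The wording also speaks of matching groups, which reads more like frequency matching than pairing. The objection does not reach the univariate step: the article names chi-square and Fisher tests for a matched comparison, and those are unmatched. The t and Wilcoxon names do not by themselves exclude paired versions.

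A reader might also infer that the denial odds ratios are bound to be attenuated. The documents do not support this. Nothing in them ties maternal attachment, personality disorder or psychiatric condition to parity or prematurity, and without such a link the bias is zero. Nor should one infer false positives: where the unadjusted standard error is off for this reason, it is too large.

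For infant outcomes, Statistical methods states no case-against-control test on a continuous score. Its t-test there compares characteristics of secure and insecure children, who are not the matched groups. A type I error or power figure for such a score test would describe an analysis that the article does not state. The Bias section already acknowledges the unequal dropout.

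**Conclusion.** The point holds in a limited form. The design is matched, the analysis text does not say that the matching is accounted for, and the categorical univariate tests it names are unmatched. For the denial analysis the possible error has a known direction (odds ratios toward 1, conservative tests) and is modest: the log odds ratio shrinks by 0 to about 10% for associations with the matching factors up to an odds ratio of 3, and by about 18% at 5. These sizes rest on assumed parity, prematurity and exposure frequencies. For infant outcomes the cost is some lost precision and a possible imbalance in the two factors after dropout, neither of which the documents allow to be quantified. The conclusion does not depend on the multivariate model actually omitting the factors: the remedy is a better-specified analysis than the crude tests now named.

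**What to change.** In Statistical methods:

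- State whether controls are matched individually or by frequency.
- Include parity (primiparous or not) and prematurity (birth before 37 weeks) as covariates in the logistic model for denial, and in every model comparing infant outcomes between cases and controls.
- Base inference on these adjusted (or stratified) estimates, and keep the crude tests as description.
- Use conditional logistic regression only if controls are individually matched.
- State that parity and prematurity will not be interpreted as factors associated with denial, since the design fixes their distribution. The article does not propose to do so; the sentence is a safeguard.

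The cost is a few lines of analysis wording. Both variables are needed for the matching, and gestation and parity are already taken from the mother's records at the first visit, so no new data are required.

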## Objectives

### Study hypothesis

We put forward the following hypothesis: an insecure attachment of the mother would participate or at least would increase the likeliness of pregnancy denial. These mothers would find it difficult (even impossible in some cases) to access the experiences of their infants, which are essential in the psychological reorganizations necessary during pregnancy to prepare the woman to accept her new functions as a mother.

Moreover, the absence or reduction of the duration of the usual 9-month period for psychological elaboration during the pregnancy calls into question its potential impact on the quality of mother-child interactions. Are there consequences on the infant’s development as well as on his pattern of attachment? We hypothesize that the attachment and the development of the infant to be born, as well as the quality of mother-infant interaction, are disturbed when the woman presents a denial of pregnancy. Specifically, we expect these consequences to be stronger with a longer duration of pregnancy denial.

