### Study objectives

The primary objective of this study is to examine the relationship between pregnancy denial and infant attachment patterns, early mother-infant interaction and early infant development.

The secondary objectives of this research are as follows:To explore among women with pregnancy denial the influence of the duration period between the pregnancy announcement and delivery on infant attachment pattern, early mother-infant interaction and early infant development;To study the factors associated with pregnancy denial, including the type of maternal attachment and the existence of a maternal personality disorder and/or a psychiatric condition.

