During the first visit (during the week after delivery), informed consent, data (demographics, age, marital status, level of education, financial resources, socio-economic data of the child’s father, developmental data of the child’s siblings) will be collected. Additionally, medical information, including gestation and parity, pregnancy records, and medical, surgical and psychiatric history, will be extracted from the mother’s charts. Direct assessment of perceived social support with the Perceived Social Support Questionnaire (PSSQ) [24] and psychiatric condition will be provided with the Mini International Neuropsychiatric Interview (MINI) for Psychiatric Disorders Axis I [25].

The second visit (6 to 8 weeks after delivery) includes the following: assessments of depression with the Beck Depression Inventory (BDI) [26] the Edinburgh Perinatal Depression Scale EPDS [27], of maternal anxiety with the Scale Trait Anxiety Inventory (STAI) [28] of personality disorders using the screening of the International Personality Disorders Examination (IPDE) [29] and of maternal attachment patterns with the Adult Attachment Narratives (AAN) [30].

The third visit (6 months after delivery) includes assessments of mother-infant interaction during a meal with the Coding Interaction Behavior system (CIB) [31, 32], of the child’s temperament with a questionnaire on the 6-month-old infant’s temperament (QT6) [33, 34], of maternal depression (EPDS) [27] of child development using the Denver Developmental Screening Test [35] and of the relational retreat behavior of the child with the Alarm Distress Baby (ADBB) Scale [36] and the semi-structured interview for personality disorders (IPDE) [29].

The fourth visit (12 months after delivery) includes evaluations of maternal depression (BDI and EPDS), of maternal anxiety (STAI), of perceived social support (PSSQ), of interactions during a meal (CIB), of child development (DSST) and of the relational retreat behavior of the child (ADBB).

The fifth visit (18 months after delivery) includes evaluations of the infant’s pattern of attachment with the SSP (Strange Situation Procedure) [35] and of the infant’s development (DSST).

The sixth visit (20 months after birth) is a free assessment with the objective of thanking the parents for their participation and surveying them about the organization and design of this study.

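### Infant attachment is analysed only as a search for associated factors; denial is not fixed as the exposure, and its coefficient can be attenuated if postnatal consequences of denial enter the same model

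*Protocol article*

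**What the plan says.** The Study objectives section states: "The primary objective of this study is to examine the relationship between pregnancy denial and infant attachment patterns, early mother-infant interaction and early infant development". This is a question about one exposure and its outcomes. The Discussion likewise speaks of the consequences of denial for the child's attachment.

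Statistical methods contains two inferential analyses. The first compares women with and without denial and models denial as the outcome, so it addresses the secondary objective on factors linked to denial. The second is the only one with infant attachment as outcome. It covers "Factors associated with the attachment pattern of the child, divided into two categories" (secure and insecure), and these factors "will be studied by univariate (Student’s t, Wilcoxon, chi-square or Fisher’s exact tests, as appropriate", followed by "and multivariate analysis (logistic regression". The paragraph names no exposure of interest and does not say whether the univariate or the multivariable result answers the primary objective.

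The Study hypothesis gives a causal ordering. The shortened period of preparation "calls into question its potential impact on the quality of mother-child interactions". The infant's attachment and development, "as well as the quality of mother-infant interaction, are disturbed when the woman presents a denial of pregnancy". For maternal attachment the order is reversed: "an insecure attachment of the mother would participate or at least would increase the likeliness of pregnancy denial".

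Under Prospective visit calendar, the Strange Situation takes place at 18 months. The 12-month visit includes assessments "of interactions during a meal (CIB), of child development (DSST) and of the relational retreat behavior of the child (ADBB", together with maternal depression, anxiety and perceived support. Interaction, development, withdrawal and infant temperament are also assessed at 6 months.

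**The concern.** A search for factors treats every candidate alike and asks which ones correlate with attachment when all are considered together. The primary objective asks how attachment differs between infants of mothers with and without denial, after allowing for what made the mothers differ beforehand. The two questions need different adjustment sets.

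Variables measured at 6 and 12 months are natural candidates in such a search. On the protocol's own hypothesis, at least interaction and development follow from denial, and they may be steps towards the 18-month result. Withdrawal, temperament and postnatal maternal state could play the same part. With any such step in the model, the denial coefficient measures only what does not pass through it. If the hypothesis is right, the pathway variables may be among the stronger correlates of attachment, and denial could then be reported as not independently associated although its total effect is real. The article does not say which result takes precedence if a crude association disappears in the joint model.

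**Working it through.** **Comparing the sections.**
- Study objectives: denial is the exposure; attachment, interaction and development are outcomes.
- Statistical methods: attachment is the outcome, with unnamed factors on the other side. That denial is one of them is inferred from the objective.
- Study hypothesis and visit calendar: interaction and development are consequences of denial and are measured before attachment. Maternal attachment is an antecedent, although its instrument is given after birth.

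Time of measurement therefore does not separate mediators from confounders; the hypothesised order does.

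**The plan's own effect size and power.** From Population: means 3.44 and 2.37, SD 1.90, two-sided 5%, 70 included and 50 evaluated per group, stated power 90%.
- Standardised difference, size only: (3.44 − 2.37)/1.90 = 1.07/1.90 = 0.563.
- Power at 50 per group: Φ(0.563/√(2/50) − 1.96) = Φ(2.816 − 1.96) = 80.4%.
- Power at 70 per group: 91.5%.

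The stated 90% is reproduced at the number included but not at the number evaluated. That is a separate matter; 80% is the baseline here.

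**Illustration 1, linear.** Assumptions not in the documents: one mediator M, shifted 0.8 SD by denial; unit variance of M and of the outcome within group; a share s of the total effect passes through M.
- Path from M to the outcome: b = s × 0.563/0.8.
- Adjusted denial effect: (1 − s) × 0.563.
- Standard error: √[(1 − b²) × (2/50) × (1 + 0.8²/4)] = √[(1 − b²) × 0.0464].

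| Share s | b | Adjusted effect (SD) | SE | Power, formula | Power, simulation (4000 runs) |
|---|---|---|---|---|---|
| 25% | 0.176 | 0.42 | 0.212 | 51% | 49% |
| 50% | 0.352 | 0.28 | 0.202 | 29% | 28% |
| 75% | 0.528 | 0.14 | 0.183 | 12% | 12% |

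Without M in the model, power is about 80%.

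**Illustration 2, logistic, as planned.** Assumptions: 50 per group, conditional log-odds effect of denial 1.2 in total, mediator log odds ratio 1.0 per SD, 1500 runs.

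| Share | Median OR, crude | Median OR, adjusted for M | Power, crude | Power, adjusted |
|---|---|---|---|---|
| 0% | 2.70 | 3.42 | 0.70 | 0.76 |
| 25% | 2.74 | 2.50 | 0.71 | 0.51 |
| 50% | 2.68 | 1.82 | 0.71 | 0.26 |
| 75% | 2.68 | 1.32 | 0.72 | 0.08 |
| 100% | 2.68 | 0.99 | 0.70 | 0.05 |

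The adjusted medians follow exp[(1 − s) × 1.2] = 3.32, 2.46, 1.82, 1.35 and 1.00. The crude odds ratio lies below 3.32 even without mediation because odds ratios are not collapsible, so the power columns are the safer comparison. With no mediation, adjustment costs nothing here. With partial mediation it attenuates, and only with complete mediation does the effect vanish.

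**The case against.** The strongest reply is that Statistical methods names no covariate and no selection rule, and does not say that any 6- or 12-month variable will be entered. A condensed article may leave the adjustment set to a full protocol or analysis plan, so the missing list is not a fault. This stands. A reader might infer that the plan does adjust the effect of denial away. The text does not support that: being collected is not the same as being entered, and the loss also requires mediation, which is hypothesised but of unknown size.

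Second, the univariate step would compare attachment between cases and controls with no mediator in the way. This also stands, so an unadjusted denial result would not be lost. It is not a sufficient answer, however. The groups are not randomised and are matched only on parity and prematurity, so the crude comparison leaves other confounding in place, including by maternal attachment, which the protocol itself proposes as a contributor to denial.

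Third, interaction and development are listed as outcomes of the primary objective, so reading them as covariates is not the kindest interpretation. That is fair, but nothing in the factor analysis keeps an outcome measured at 6 or 12 months out of the model for one measured at 18 months.

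Fourth, the power figures rest on assumed shares and a single assumed mediator, and the linear version uses a continuous score where the plan specifies a binary one. They show the direction and possible scale of the problem and do not predict what this study will find.

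**Conclusion.** The point holds as a mismatch between objective and analysis, with a conditional risk attached. The article does state an analysis for infant attachment, and its type does not fit the primary objective: it looks for correlates and does not set denial as the fixed exposure. That goes beyond an unlisted covariate set.

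The risk is that postnatal consequences of denial enter the one multivariable model and turn the denial coefficient into a residual direct effect. Its size cannot be derived from the documents. Under the linear assumptions, power falls from about 80% to about 49%, 28% or 12% when 25%, 50% or 75% of the effect is mediated. The logistic version shows the same pattern.

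A change is advisable, with medium confidence. It should not be read as meaning that every variable measured after birth is a mediator, since maternal attachment and arguably personality disorder belong among the antecedents.

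**What to change.** Replace the single factor analysis of infant attachment with two labelled models.

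(A) For the primary objective, regress infant attachment on denial group, forced in as the exposure. Adjust for the matching factors (parity, prematurity) and for antecedents of denial: age, education, marital status, psychiatric history, maternal attachment and personality disorder. Exclude the 6- and 12-month measures of interaction, development, withdrawal, temperament and maternal mood. State that this model answers the primary objective for attachment.

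The adjustment set has to be short. About 100 evaluated dyads give at most 50 in the smaller outcome class. Denial plus all eight covariates, at one coefficient each, is nine coefficients, so at most 50/9 ≈ 5.6 outcomes per coefficient. The antecedents should be ranked or reduced before the data are seen.

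(B) In a separate exploratory pathway model, add the postnatal variables. State that it is not used to decide whether denial is related to attachment.

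The cost is wording and one extra model, with no change to data collection. Two denial estimates will have to be explained. Because maternal attachment and personality disorder are assessed after birth and might themselves be affected by the experience, a sensitivity analysis of model A without them is advisable.

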### Measures

For the infants: The attachment pattern of the infant is assessed with the Strange Situation Procedure [37, 38] A mother and an 18-month-old infant are under observation in a laboratory. The observer notes the child’s reactions during 8 episodes of 3 minutes involving the separations and reunions between the mother and the child, as well as the introduction of a stranger. The situation is videotaped. The coding system of interactive behaviors allows a categorization into 4 attachment patterns: “secure”, “anxious-avoidant insecure”, “anxious-resistant insecure” and “disorganized/disoriented insecure” (regrouped into two categories: “secure” and “insecure”). Richters and associates [39] developed a method to score attachment in a continuous way. Van IJzendoorn and Kroonenberg [23] adapted and validated the algorithm for use with Strange Situation interactive scales without scores for crying. The resulting algorithm yields a continuous score for attachment that is strongly associated with the insecure vs. secure attachment classifications. Higher security scores indicate a more secure attachment relationship. Continuous scores for disorganization were derived directly from coding the conventional 9-point scale for disorganization [40], with higher scores indicating more disorganized behavior.

The quality of early mother-infant interaction is assessed with the Coding Interactive Behavior (CIB) of Feldman [31, 32]. The CIB includes 42 items (21 concerning the mother, 16 concerning the child and 5 concerning the dyad). Each item is evaluated on a 5-point scale. During the first year, 6 dimensions are extracted from the CIB items: (i) parental sensitivity, (ii) parental intrusion, (iii) infant’s social engagement, (iv) infant’s negative emotionality/infant’s engagement, (v) dyadic reciprocity and (vi) dyad’s negative states. The scale consists of 2 segmentations of 15 minutes of interactions: one session of a game and one session of feeding. The 6-month-old infant’s temperament is assessed with the French version of the Infant Characteristics Questionnaire of Bates [33]. The QT6 is a self-questionnaire administered to the mothers with 26 questions about the “difficult” temperament of the infant. It was validated in France with 794 mothers of infants aged 6 to 9 months [34].

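### The sample size rests on the continuous disorganization score, but the only infant analysis stated is of a different variable, the secure/insecure split

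*Protocol article*

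**What the plan says.** The sample size paragraph of the Population section opens with "Based on the hypothesis of a score for disorganization [22, 23] of 3.44 ± 1.90 in the control group". It then says that the planned numbers "will highlight a score for disorganization of 2.37 in the case group", "with a signification of 5%, a power of 90% and a bilateral". The numbers are given as "inclusion of 70 dyads mother-infant per group (and evaluation of 50 dyads at 18 months because of lost of follow up".

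The Measures section describes three ways to express the Strange Situation result: a four-pattern classification regrouped into secure and insecure, a continuous security score, and a disorganization score. On the last it says: "Continuous scores for disorganization were derived directly from coding the conventional 9-point scale for disorganization". Higher values mean more disorganized behaviour.

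The Statistical methods section covers one infant outcome: "Factors associated with the attachment pattern of the child, divided into two categories". The methods named are univariate tests (Student, Wilcoxon, chi-square, Fisher) and logistic regression. The other paragraph on comparisons concerns the women's characteristics by denial status.

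**The concern.** The sample size calculation and the stated analysis use different variables. The calculation is for a difference in means on a 9-point scale. The analysis is of a two-category outcome in which disorganized infants are pooled with avoidant and resistant ones.

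Two things follow. The claimed power says nothing about the one infant analysis that the article states, so a null secure/insecure result could not be read against it. And the score that justifies the sample has no stated case-control comparison. The Student and Wilcoxon tests in the Statistical methods section do not fill that gap, because they compare women's characteristics by denial status or candidate factors by secure/insecure status.

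**Working it through.** **Inputs from the Population section.** Control mean 3.44, SD 1.90; case mean 2.37; two-sided 5%; stated power 90%; 70 per group included and 50 evaluated at 18 months (read as 50 per group). Assumption: the SD is the same in both groups.

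**Step 1. Standardized difference.** (3.44 − 2.37) / 1.90 = 1.07 / 1.90 = 0.563.

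**Step 2. The plan's own figure.** For a two-sample t-test the noncentrality is 0.563 × √(n/2).
- n = 70 per group: 0.563 × √35 = 3.33; power 91.1% (normal approximation 91.5%).
- n = 50 per group: 0.563 × √25 = 2.82; power 79.6% (normal approximation 80.4%).
- 90% needs 67 evaluated per group by the normal approximation, 68 by the t-test.

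The stated 90% is thus reached if all 70 per group are analysed, but not with the 50 expected at 18 months. The right baseline for judging the split is about 0.80. The step from 90% to 80% comes from attrition and has nothing to do with dichotomizing.

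**Step 3. Power of the split, as an illustration.** The document gives no secure/insecure rates. Suppose that the split is a cut on a latent normal variable carrying the same 0.563 SD shift. With p0 the proportion insecure among controls, the case proportion is p1 = Φ(Φ⁻¹(p0) ± 0.563). The plus sign makes cases more insecure, as the Study hypothesis section expects. The minus sign follows the direction of the sample size figures, where cases score lower. Power of the chi-square test (two-sided 5%, 50 per group, exact enumeration):

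| p0 | p1, cases more insecure | power | p1, cases less insecure | power |
|---|---|---|---|---|
| 0.20 | 0.390 | 0.557 | 0.080 | 0.431 |
| 0.30 | 0.515 | 0.608 | 0.138 | 0.509 |
| 0.35 | 0.571 | 0.626 | 0.171 | 0.539 |
| 0.40 | 0.622 | 0.630 | 0.207 | 0.560 |
| 0.50 | 0.713 | 0.601 | 0.287 | 0.601 |

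The range is 0.43 to 0.63, against 0.796 for the continuous score with the same 50 per group.

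**The case against.** The article condenses a fuller protocol, and an analysis plan may exist. The Statistical methods section is short and states no analysis of mother-infant interaction or infant development, although both belong to the primary objective ("infant attachment patterns, early mother-infant interaction and early infant development"). It is plainly not a full list, and a comparison of disorganization scores may be planned elsewhere. This stands in part. A reader might infer that the sized endpoint will never be tested, but the document supports only that no such test is stated here. The mismatch remains all the same: the section is not silent on infant attachment, but states an analysis of a variable other than the one sized.

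A second objection concerns the power figure. If the split is a different construct, the effect size for disorganization need not carry over to it. This stands. A reader might conclude that power falls to about 60%, but that figure needs an assumed effect transfer, an assumed control rate and a chosen direction. A reader might also blame the split for a whole fall from 90% to 60%, when the first ten points come from evaluating 50 rather than 70 per group.

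A third inference is that the three-domain primary objective creates a large, countable multiplicity problem. The interaction and development tests that such a count would need are not listed in the Statistical methods section, and handling of multiplicity is commonly left to the analysis plan. It is not part of this point.

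**Conclusion.** The concern holds in this form: the sample size is justified on the continuous disorganization score, the only infant analysis stated is of the secure/insecure split, and the stated power does not apply to that analysis. This follows from the text alone and needs no assumption.

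The size of the power loss is conditional. Under the same latent shift of 0.563 SD, 50 per group and control insecurity of 20% to 50%, power for the split is about 0.43 to 0.63, against about 0.80 for the score itself. If the effect on the pooled insecure category differs from the effect on disorganization, the true figure could lie outside that range. In every case computed under this model, the split has clearly less power than the score.

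**What to change.** Reconcile the Population and Statistical methods sections. State the 18-month continuous disorganization score as the primary attachment endpoint. Compare it between cases and controls at two-sided 5% with a linear model that includes denial status and the matching factors (parity and prematurity), or with a rank-based test if the score is skewed. Keep the secure/insecure logistic regression as a secondary analysis.

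The cost is wording only, because the score comes from the Strange Situation already planned at 18 months. The downside is that the binary classification loses its lead position.
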